#### Korean Mann Assessment of Swallowing Ability (K-MASA)

The K-MASA is the Korean-validated version of the MASA tool, which is a bedside examination for the evaluation of dysphagia that has been validated in first-time stroke patients (37). MASA assesses 24 skills related to sensory and oral motor elements of swallowing. Performance for each skill is measured using a 5- or 10-point rating scale and tallied to create a total numeric score out of 200 possible points, which are interpreted as no abnormality (≥178), mild dysphagia (168–177), moderate dysphagia (139–167) and severe ( ≤ 138) (38). K-MASA will be assessed at the past mentioned 4 outcome periods.

#### Gugging Swallowing Screen (GUSS)

GUSS is a bedside dysphagia screening tool for patients with stroke of easy use for nurses and therapists, that can identify stroke patients with dysphagia and aspiration risk and also can be helpful in choosing dietary prescriptions for the patients. The assessment comprises two parts, the preliminary assessment (indirect swallowing test) and the direct swallowing test, which consist of 4 items with 3 subtests (semisolid, liquid and solid). The test is based on a pointing system where higher numbers denote better performance, with a maximum of 5 points that can be reached in each subtest. Twenty points are the highest score a patient can attain, and it denotes normal swallowing ability without aspiration risk (39). The GUSS will be assessed at Baseline, Mid-intervention, Post-intervention, and Follow-up.

#### Eating Assessment (EAT-10)

The EAT-10 is a tool to assess self-perceived symptoms of oropharyngeal dysphagia and monitor changes in response to a treatment (40). It consists of ten items to be rated on a 5-point response scale (0–4), with “0” = No problem and “4” = Severe problem, the maximum score possible is 40. The validated Korean version of the EAT-10 will be used in this trial (41). The EAT-10 will be assessed at Baseline, Mid-intervention, Post-intervention and Follow-up.

#### Motor-Evoked Potential (MEP)

MEPs are a standard tool for non-invasive quantification of cortical excitability. The cortical excitability of the area corresponding to the swallowing movement will be assessed by changes in the amplitude and latency of the MEPs by using transcranial magnetic stimulation (TMS). The MEP responses of the mylohyoid and thenar musculature will be recorded. The MEP will be induced by the application of TMS over the motor cortex, the coil will be placed at an angle of 45° to the parasagittal plane, tangential to the scalp surface, since this is the ideal orientation for evoking both swallow and thenar muscle response, the stimuli will be applied bilaterally (42). Resting motor thresholds, amplitude, and latency of evoked potentials will be measured before and after the TMS brain stimulation. MEP will be assessed during Baseline, Mid-intervention and post-intervention.

### DTI-based assessment of corticobulbar tract

The corticobulbar tract's white matter integrity is crucial for optimal swallowing function, with empirical evidence showing that damage to these tracts significantly exacerbates dysphagia severity (43, 44). Moreover, white matter demonstrates a high capacity for neuroplastic potential, as structural and functional reorganization can be observed following targeted neuromodulator interventions. Therefore, we will conduct a comprehensive quantitative analysis to systematically evaluate tDCS-induced neuroplastic changes. Specifically, diffusion tensor imaging (DTI) will be acquired at baseline and post-intervention, enabling 3D tract reconstruction and quantitative assessments (e.g., fractional anisotropy, mean diffusivity) of the corticobulbar tract.

### Iowa Oral Performance Instrument (IOPI)

The IOPI is a standardized portable device that is used to quantify tongue and lips isometric strength and endurance. It consists of a pressure transducer and an amplifier that displays on a screen, in kilopascals (kPa), the pressure exerted on an air-filled bulb. The device can measure the pressures applied by the tongue on the bulb after inserting the air-filled balloon inside the mouth and pressing the bulb against the roof of the mouth. The lips exerted pressure in kPa, can be obtained by pressing the air-filled bulb between the lips (45, 46). The IOPI will be assessed only at the Baseline, Post-intervention, and Follow-up.

### Ancillary respiratory stage assessment

The ancillary respiratory stage assessment will be performed to assess the function of the pharyngeal phase. The voice quality will be assessed by the GRBAS (grade, roughness, breathiness, asthenia, strain) scale (47) and Wet voice quality (48). The respiratory muscle strength will be assessed by measuring the maximal inspiratory and expiratory pressure using spirometry (49, 50); and the cough strength will be evaluated by the voluntary peak cough flow (51). These parameters will be assessed only at the Baseline, Post-intervention and Follow-up.

### Speech Mechanism Screening Test (SMST)

The SMST evaluates the oral function by assessing the structure and function of the articulatory system, the coordination process, and the maximum speed, regularity, and accuracy of the muscles that make up the articulatory system. The test consists of 13 questions to evaluate the structure of the articulatory system, including the face, lips, tongue, jaw, teeth, oral cavity, soft palate, pharynx, and breathing; 17 questions to evaluate the function of the articulatory system; 3 questions to auditorily evaluate the structure and function of the vocal system; and 14 questions to evaluate the regularity and articulation accuracy of the mutual movement of the articulatory system during articulatory alternation. The phonation-voice and articulation screening assess the maximum phonation time (MPT) for the/a/vowel. It assesses the pitch, loudness, speech rate, and voice quality during spontaneous name and address production and reading of a given sentence. Articulation errors and alternating movement rate (AMR) and serial movement rate (SMR) are measured to screen for functional or neurological coordination system abnormalities in articulation production, and test items in each area are scored and evaluated (52). The SMST will be assessed only at Baseline, Post-intervention and Follow-up.

### Urimal Test of Articulation and Phonology (U-TAP)

U-TAP is a test designed for native speakers of the Korean language. It is aimed at evaluating the pronunciation produced in words and sentences by patients with speech sound disorders who have problems with consonants or vowel sounds. It is recorded by phonological words and syllable position and calculates consonant accuracy and word-level phonological indices (PWC, PMLU, PWP) at the word and sentence levels to compare with normal articulation development (53). The U-TAP will be assessed only at Baseline, Post-intervention, and Follow-up.

### modified Rankin Scale (mRS)

mRS is used to assess the changes in activity lifestyle after stroke. It is composed of a 6-point assessment that includes reference to both activity limitations and lifestyle changes. The mRS possible scores vary from 0 (no symptoms) to 6 (dead) points (54). The mRS will be assessed at the Baseline, Mid-intervention, Post-intervention, and Follow-up.

### Quality of life index

The EuroQoL five-dimensional instrument with five levels (EQ-5D-5L) will assess the participants' quality of life. EQ-5D-5L consists of five dimensions of health: mobility, self-care, usual activities, pain/discomfort, and anxiety/depression. Each has five levels or response categories: no problem, slight problems, moderate problems, severe problems and extreme problems (55). The health states are defined by combining one level from each of the five dimensions, for 3,125 possible health states. For example, “11111” indicates no problems on the five dimensions. In contrast, “11125” indicates no problems with mobility, self-care, and usual activities, but slight issues with pain/discomfort and extreme anxiety/depression. The questionnaire has been validated for the general Korean population (55). The EQ-5D-5L will be assessed at Baseline, Mid-intervention, Post-intervention and Follow-up.

### General health

A general health examination will be performed during the four mentioned periods. The examination will be composed of a combination of various tests, which include nutritional examination (blood sample recollection of albumin and protein) (56), evaluation of the presence of low skeletal muscle index (56, 57), and immunologic tests (number and type of infections, white blood cell count and antibiotic use history) (58).

### Correlation between cortical E-field over the stimulated area and MEP, FOIS and PAS

To determine if there is a lineal association between the E-field generated at the Baseline by the Optimized electrode location and the results of the MEP, FOIS and PAS.

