This double-blind, randomized pilot trial aims to determine the feasibility and safety of optimized transcranial direct current stimulation (tDCS) in patients with post-stroke dysphagia. Specifically, we will (1) evaluate the feasibility of using small-sized and optimized electrode placement to maximize E-field strength in the swallowing motor cortex—comparing active vs. sham stimulation, and (2) assess the clinical safety of this approach in post-stroke dysphagia patients.

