### Randomization

Participants will be randomized using a block randomization method stratified by stroke chronicity (subacute vs. chronic) and age (19–64 vs. ≥65 years). Allocation will be concealed in opaque envelopes; a blinded investigator will assign participants (1:1) without involvement in outcome assessments.

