### Intervention

#### Individualized 3D brain modeling and optimized electrode location calculation

Each participant will undergo a comprehensive process to ensure the precise targeting of the swallowing motor cortex using tDCS. To achieve this, individualized 3D brain models will be generated for all participants using the software NEUROPHET tES LAB (Neurophet, Seoul, Republic of Korea). At the baseline of the trial, every participant will take a T1-weighted magnetic resonance imaging (MRI) scan, which will serve as the foundation for the creation of the personalized brain model. The software is designed to analyze and segment the T1-weighted MRI data, thereby constructing a detailed 3D model that accurately reflects the unique anatomical structure of each participant's brain. In addition, the software assigns pre-programmed electrical conductivity values to the various brain tissues, including the skin (0.465 S/m), skull (0.010 S/m), cerebral and cerebellar gray matter (0.276 S/m), cerebral and cerebellar white matter (0.126 S/m), cerebrospinal fluid and ventricle (1.65 S/m) and the stroke lesion area (0.809 S/m), ensuring that the simulation closely mimics the physiological properties of each individual's brain.

Both the Optimized-tDCS and the Sham group will utilize personalized, optimized electrode locations calculated using the NEUROPHET tES LAB. On the 3D brain model of each participant, the investigator will select the target region within the swallowing motor cortex of the non-lesional hemisphere where the E-field is intended to be maximized. Target selection of the swallowing motor cortex target; located in the precentral gyrus, will be made based on convergent evidence from task-based functional MRI studies of volitional swallowing (27). Cortical representation of swallowing exhibits well-documented somatotopic organization: lateral regions correspond to mylohyoid function, while medial zones associate with pharyngeal control (28–30). To balance anatomical specificity with computational feasibility, we will operationalize the target as a 2-mm radius spherical region of interest (ROI) in standardized space, positioned at the centroid between these functional activation sites.

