### Sample size estimates

Due to the feasibility nature of the study, the primary goal is to evaluate the safety, practicability, and preliminary effects of optimized tDCS stimulations with personalized electrode placement in patients with post-stroke dysphagia. Consistent with established guidelines for feasibility and pilot studies, a formal power calculation for efficacy was not performed. Instead, the sample size of 30 participants (15 per group) was determined based on practical considerations and precedent from previous studies in this field. Specifically, a similar previous study (16) demonstrated protocol feasibility and observed clinically relevant improvements in swallowing function among 28 participants (14 per group) undergoing a 20-session tDCS intervention. Our study adopts a comparable intervention schedule and aims to provide reliable estimates of key feasibility outcomes-including recruitment rates, adherence, and adverse event profiles-while also generating preliminary data on the variability and potential effect size of our primary and secondary outcome measures. These findings will be essential for informing the design and sample size calculation of a future, large-scale randomized controlled trial.

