Past research has used anodal tDCS over the lesioned side to treat dysphagia, finding improvement in the swallowing function (60, 61). Targeting the ipsilesional side might increase the activity of the lesional hemisphere and decrease the transcallosal inhibition exerted by the contralesional hemisphere, which is believed to be hyperactive after stroke (61). Additionally, some studies have suggested that targeting the ipsilesional motor region could reactivate intact portions of the motor cortex (62). Other research has shown that after stroke, compensatory reorganization of the contralesional hemispheric projections influences the recovery of swallowing function and therefore, some studies have applied anodal stimulation to the contralesional side (15, 63). Both anode locations have been shown to affect the improvement of the swallowing function positively. Based on evidence from Suntrup et al. (64), that post-stroke dysphagia recovery involves neuroplasticity in the intact hemisphere, we will apply anodal tDCS to the non-lesional hemisphere to enhance swallowing function.

While current research has shown the potential of tDCS for improving swallowing dysfunction in post-stroke dysphagia patients, to the best of our knowledge, research has yet to consider individual brain anatomical structure when determining the optimal tDCS electrode placement for tDCS intervention protocols in these patients. According to research, the conventional approach involves using the 10–20 EEG system to position tDCS electrodes over the cortical swallowing area, typically by identifying the midpoint between C3 and T3 or C4 and T4 (depending on the lesioned hemisphere) to stimulate the swallowing cortex. However, the 10–20 EEG system placements, although approximations to the targeted area, do not account for inter-individual variations in brain structures, such as skull thickness and gray and white matter integrity (65). Calculating an optimized electrode location offers a personalized electrode setting per participant, giving the exact location predicted to generate the maximum E-field over a targeted area.

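### The planned E-field correlation states no contrast with sham, so it cannot separate a field effect from anatomy or prognosis

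*Protocol article*

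**What the plan says.** The section on the correlation between cortical E-field and MEP, FOIS and PAS (protocol article, end of the outcomes) consists of one stated aim, namely to examine the "lineal association between the E-field generated at the Baseline by the Optimized electrode location and the results of the MEP, FOIS and PAS". It gives no analysis population, covariate or comparison between arms. The Statistical analysis section lists no E-field analysis; its repeated measures ANCOVA uses baseline as covariate and has no E-field term.

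On the montage, the Intervention section says: "Both the Optimized-tDCS and the Sham group will utilize personalized, optimized electrode locations". The section on transcranial direct current stimulation then separates the arms by current only: 2 mA is held for 30 minutes in the active arm, while sham gets the ramps without the sustained current. Table 1 schedules the E-field assessment at baseline, and FOIS, PAS and MEP at baseline, mid-intervention and post-intervention, without distinction by arm.

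The first aim in the Introduction concerns the feasibility of small electrodes and optimised placement to "maximize E-field strength in the swallowing motor cortex—comparing active vs. sham stimulation". The Discussion treats superiority over sham as showing that optimised locations are feasible.

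**The concern.** The modelled E-field is a baseline characteristic of the patient's head under the chosen montage. Every participant has a value, but only the active arm is exposed to that field for the session. The plan does not say which patients enter the correlation, and both possible readings have a fault.

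- **Active arm only:** patients with different anatomy are compared with nothing to show how such patients would have fared without current.
- **Both arms pooled:** sham patients carry a 2 mA field that they do not receive beyond the ramps. A real effect is diluted, and a prognostic association is picked up with twice the sample.

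In either case an association produced by anatomy could be reported as if a stronger field gave better swallowing. The Sample size section says the results will inform a larger trial, so such a finding would carry forward. FOIS and PAS are also ordinal scales (7 and 8 levels), for which a linear coefficient is a weak summary.

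**Working it through.** **1. The plan's own figure.** 15 + 15 = 30, which agrees. Nothing else can be reproduced: the Sample size section says "a formal power calculation for efficacy was not performed", and no alpha, effect size or SD is given. Two-sided 0.05 is assumed below.

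**2. The confounding path in the article's own text.** The Introduction says that lesion size, shape and location affect the E-field distribution, and that individual anatomy affects the field pattern. It also says that dysphagia severity is related to stroke location and lesion volume, and that atrophy and white matter changes can impair swallowing recovery. The same anatomy can therefore drive both predictor and outcome. The strength of the link is not stated, so a range is used.

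**3. False associations with no field effect.** 20,000 simulated trials per setting, 15 per arm. E is standard normal and Y = ρE + √(1 − ρ²)·e in both arms, so current does nothing. The interaction is tested in a linear model with arm, E and E × arm. Share of trials with p < 0.05:

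| Assumed ρ | Active only (n = 15) | Pooled (n = 30) | E × arm |
|---|---|---|---|
| 0 | 5% | 5% | 5% |
| 0.2 | 11% | 19% | 5% |
| 0.3 | 19% | 37% | 5% |
| 0.4 | 33% | 62% | 5% |
| 0.5 | 50% | 83% | 5% |

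The interaction keeps its level because arm is randomised: without an effect of current, the expected slope on E is the same in both arms, whatever its cause.

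**4. Dilution when the field does work.** With a slope of 0.5 in the active arm, none in sham and ρ = 0, the test is significant in 41% of trials (active only), 25% (pooled) and 24% (interaction).

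**5. Precision of a single correlation.** Fisher interval: tanh(atanh r ± 1.96/√(n − 3)). For r = 0.5:
- n = 15: 0.549 ± 1.96/√12 = 0.549 ± 0.566, giving −0.02 to 0.81.
- n = 30: 0.549 ± 1.96/√27 = 0.549 ± 0.377, giving 0.17 to 0.73.

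**6. Power for a difference between arms.** SE = √(1/12 + 1/12) = 0.408, and power ≈ Φ(atanh(r)/0.408 − 1.96) for r in active against 0 in sham. For r = 0.5: Φ(1.345 − 1.96) = 27%. For r = 0.3 it is about 12%, and for r = 0.7 about 57%. For 80% power, atanh(r) must be (1.96 + 0.84) × 0.408 = 1.144, so r = 0.82.

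**The case against.** The strongest reply is that the section states an aim, not a model. Population, covariates and interaction terms may stand in an analysis plan that is not shown. That is fair as far as it goes: nothing in the article says that sham will be left out as a control. What remains is that the aim as worded is a plain association, and neither way of carrying it out answers the question it raises.

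A reader might go further and infer that the E-field aims cannot be answered at all because both arms get an optimised montage. The documents do not support this. The first aim is about feasibility, and maximising the field is the purpose of the placement, not a hypothesis that the field differs by arm. Feasibility and safety can be described, and active against sham is a valid randomised test of current. Optimised positions in sham are good design: they support blinding and supply the control slope.

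Three further points stand in part:
- The target is in the non-lesional hemisphere, which may weaken the lesion route. The atrophy route remains.
- The false-positive rates depend on an assumed correlation. They rise at every non-zero value tried, but no single value should be quoted as the risk.
- The analysis is a secondary item in an exploratory trial, claims only association, and leaves the primary comparison of FOIS and PAS untouched.

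**Conclusion.** The point holds for the E-field correlation. As worded it does not separate an effect of the field from anatomy or prognosis. With no field effect and an assumed prognostic correlation of 0.2 to 0.5, a false association appears in about 11% to 50% of trials (active only) or 19% to 83% (pooled), against about 5% for the interaction. These rates rest on that assumed range, a continuous outcome, two-sided 0.05 and 15 analysable patients per arm.

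The interaction is better, but at this size it gives an estimate and not a decision. Since the field itself is not randomised, even a clear difference in slopes would show only that response to current varies with the modelled field.

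A lesser point of wording also holds. There is no conventional-montage comparison, so a benefit over sham would not show that optimisation or the small electrode contributed to it. The first aim and the Discussion can be read as if it would.

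**What to change.** 1. Replace the correlation with an exploratory model of the post-intervention score on baseline score, arm, E-field and E-field × arm, with the sham slope as negative control. Report the slope in each arm and their difference with a 95% confidence interval. Give rank-based coefficients by arm for FOIS and PAS, and avoid causal wording.
2. Reword the first aim and the matching sentence in the Discussion so that active against sham is described as a test of active current at an optimised montage, not of optimisation or electrode size.
3. Optional: simulate a conventional montage on each existing head model and report the paired difference in target E-field (up to 30 pairs). The Discussion describes the usual stimulation site, "typically by identifying the midpoint between C3 and T3 or C4 and T4", and the usual 25 cm² electrode, but gives no return-electrode position, so one would have to be stated. Changing site and size together would not separate their contributions.

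Items 1 and 2 need only text, since the data are already scheduled in all participants. The price of item 1 is a wide interval at 15 per arm. Item 3 costs one extra simulation per participant.

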### Sample size estimates

Due to the feasibility nature of the study, the primary goal is to evaluate the safety, practicability, and preliminary effects of optimized tDCS stimulations with personalized electrode placement in patients with post-stroke dysphagia. Consistent with established guidelines for feasibility and pilot studies, a formal power calculation for efficacy was not performed. Instead, the sample size of 30 participants (15 per group) was determined based on practical considerations and precedent from previous studies in this field. Specifically, a similar previous study (16) demonstrated protocol feasibility and observed clinically relevant improvements in swallowing function among 28 participants (14 per group) undergoing a 20-session tDCS intervention. Our study adopts a comparable intervention schedule and aims to provide reliable estimates of key feasibility outcomes-including recruitment rates, adherence, and adverse event profiles-while also generating preliminary data on the variability and potential effect size of our primary and secondary outcome measures. These findings will be essential for informing the design and sample size calculation of a future, large-scale randomized controlled trial.

